##### Wake After Sleep Onset (WASO)

WASO measures the cumulative amount of time (in minutes) a participant spends awake after initially falling asleep until final morning awakening. Elevated WASO values may indicate fragmented or disrupted sleep, which can negatively affect sleep quality and daytime functioning. It is automatically computed by summing detected wake periods within the sleep period time by the MUSE device algorithm.

### Secondary Outcomes Measures

#### Overview

In addition to the objective measures of sleep, the study will assess several secondary outcomes that capture participants’ subjective experiences, intervention adherence, and device usability.

#### Total Sleep Time (TST)

Total sleep time (TST) is the total amount of time spent asleep during the night, excluding any periods of wakefulness after sleep onset. It reflects the overall quantity of sleep and is a core indicator of sleep sufficiency. Derived directly from the MUSE’s sleep stage classification, summing up the total minutes spent in light, deep, and REM sleep stages.

#### Sleep Efficiency (SE)

Sleep efficiency (SE) is the percentage of time in bed actually spent sleeping. It is calculated by dividing TST by the total time spent in bed and multiplying by 100. Higher SE suggests less wakefulness during the night and better overall sleep quality. SE is calculated automatically by the MUSE device algorithm.

#### Sleep Stages

The EEG data will be analyzed to determine the time spent in different sleep stages: REM (rapid eye movement) sleep, deep sleep (slow-wave sleep), and light sleep. These are expressed in percentages.

#### Subjective Sleep Quality

Each morning, participants will complete a low-burden Single-Item Sleep Quality Scale, a validated tool designed to assess overall perceived sleep quality [24]. We chose this brief item to minimize burden and support daily completion in older adults. This brief measure captures participants’ evaluations of how well they slept the previous night, ranging from 0 (terrible) to 10 (excellent). Subjective ratings are analyzed alongside objective EEG outcomes as complementary indices of sleep and are tested across passive ETU, active ETU, and nondigital activity.

#### Intervention Adherence and Perception

Participants will be asked whether they were able to complete the assigned evening activity the previous night. If the answer is “yes,” they will also report how long they engaged in the intervention (in minutes). This self-report measure will help evaluate the feasibility and real-world compliance with each intervention condition.

To assess how participants perceived each evening activity, they will complete a brief daily rating scale immediately after the intervention. The scale includes 5 items rated from 0 (not at all) to 10 (extremely), adapted from established tools: the Visual Analog Mood Scales for calmness [25], the Positive and Negative Affect Schedule for enjoyment and stress [26], and the User Engagement Scale for engagement and perceived meaningfulness [27]. This approach allows for low-burden, repeated assessment of affective and cognitive responses relevant to sleep-related outcomes in older adults. The survey is included in MultimediaAppendices 2  3. The internal consistency of the items (Cronbach α), once the data is collected, will be reported in the main study.

#### Comfort Level of EEG Headband

To assess usability and participant burden, participants will rate the comfort of wearing the EEG headband during the night using a 5-point Likert scale. The scale ranges from 1 (very uncomfortable) to 5 (very comfortable). This data will inform the acceptability of the MUSE EEG headband as a sleep monitoring tool and identify any potential discomfort that may influence sleep or compliance.

### Statistical Analysis Plan

Analyses will be conducted in SPSS Statistics (version 29.0.x; IBM Corp, Armonk, NY); the exact patch (eg, 29.0.2) will be reported at analysis. Descriptive statistics will be used to summarize demographic information, baseline sleep characteristics, chronotype prevalence, overall intervention adherence (percentage of nights completed; minutes engaged), perception ratings (calmness, stress, engagement, enjoyment, meaningfulness on 0‐10), and EEG headband comfort (1‐5 Likert), presented as mean (SD) or median (IQR), as appropriate.

Primary and secondary sleep outcomes will be derived from MUSE EEG auto-scoring using the device’s standard algorithm. This study does not include manual rescoring or a new polysomnography comparison; instead, we rely on published validation studies demonstrating agreement with polysomnography/manual scoring [28,29]. All analyses will use participant-level week means (nightly values averaged within each intervention week/condition). Before analysis, we will check data quality. A night is classified as VALID if the device records ≥4 hours within the main sleep window and yields plausible values (eg, TST 2‐12 h, SOL 0‐180 min, WASO 0‐240 min); otherwise, it is INVALID. All the valid nights will be included in the analysis. During the analysis, the data analyst will be blinded to intervention allocation. Unblinding will occur only after the analysis code is finalized, outputs are generated, and the primary results are locked. Participant-level week means (nightly values averaged within each intervention week/condition) will be calculated for descriptive purposes.

The coprimary outcomes are SOL and WASO derived from the MUSE EEG. The primary objective compares combined ETU versus nondigital activity, where ETU is defined by collapsing the 2 technology conditions (passive and active) into a single ETU category. This will be tested as a prespecified linear contrast of the condition marginal means from a linear mixed-effects model (LMM). For each primary outcome (SOL and WASO), we will fit an LMM with fixed effects for condition and period and a participant-specific random intercept. The LMM analyses will use all available valid nights. In addition to the prespecified combined-ETU contrast, we will estimate all pairwise condition contrasts (active vs passive, active vs nondigital, passive vs nondigital) using the Tukey adjustment. Model-based estimates, 95% CIs, and *P* values will be reported, together with a standardized within-participant effect size. Multiplicity control across the 2 coprimary endpoints (SOL and WASO) will be performed using the Holm procedure with a family-wise α of .05 (2-sided). If at least one coprimary endpoint is statistically significant after the Holm adjustment, we will proceed to confirmatory testing of the prespecified key secondary outcomes; otherwise, these secondary outcomes will be reported as exploratory. Model assumptions will be checked; if needed, outcomes will be transformed or analyzed using an appropriate generalized mixed model.

Key secondary objective outcomes are TST, SE, and sleep stages (REM%, Deep% [SWS], Light%). These outcomes will be analyzed using the same LMM framework (fixed effects for condition and period; random participant intercept), with Tukey adjustment for pairwise condition comparisons. To control for multiplicity across the key secondary outcomes, *P* values will be adjusted using Holm’s procedure (2-sided α=.05), applied only if the gatekeeping criterion on the coprimary outcomes is met. All remaining outcomes (eg, subjective sleep, adherence, and comfort) will be treated as exploratory and interpreted primarily via effect estimates and 95% CIs.

We will briefly explore how subjective sleep aligns with objective measures using simple descriptive statistics (mean, SD and median, IQR). The full analysis code will be included as a supplementary file (including SPSS syntax and output) when the main study is reported. The statistical plan for each research question is presented in Table 1.

**Table 1. T1:** Research questions with hypotheses, planned analysis, and expected endpoints.

Objectives	Research question	Hypothesis (H₁)	Null hypothesis (H₀)	Endpoints and analysis
Primary objective	Does evening technology use (ETU) affect primary objective sleep outcomes (WASO^a^ and SOL^b^) compared with engaging in nondigital activity like reading physical books?	Older adults exposed to ETU before bedtime will show significant impairments in primary objective sleep outcomes than those exposed to nondigital activity.	Older adults exposed to ETU before bedtime will show no significant impairments in primary objective sleep outcomes than those exposed to nondigital activity.	Primary outcomes: SOL, WASO (MUSE EEG)^c^. Linear mixed-effects model with fixed effects for condition and period and a random participant intercept. Multiplicity across SOL and WASO controlled using Holm (α=.05, 2-sided). Pairwise condition comparisons reported with Tukey adjustment. Report estimated marginal mean 95% CIs, *P* values, and Cohen *d* (standardized within-participant effect sizes).
Key secondary	Does passive ETU^d^ lead to better objective sleep outcomes than active ETU?	Passive ETU will show significant differences in sleep outcomes than active ETU.	Passive ETU will lead to no difference in sleep outcomes than active ETU.	SOL, WASO, SE^e^, TST^f^, Sleep Stages (REM%^g^, Deep%, Light%). LMM^h^ with fixed effects for condition and period and a random participant intercept. Confirmatory testing follows a hierarchical (gatekeeping) strategy: these outcomes are formally tested only if ≥1 coprimary endpoint is significant after Holm adjustment. Multiplicity across key secondary outcomes controlled using Holm (α=.05). Pairwise condition comparisons use Tukey adjustment.
Key secondary	Does passive ETU lead to better objective sleep outcomes than nondigital activity^i^?	Passive ETU will show significant differences in sleep outcomes than nondigital activity.	Passive ETU will show no significant differences in sleep outcomes than nondigital activity.	SOL, WASO, SE, TST, Sleep Stages (REM%, Deep%, Light%). LMM with fixed effects for condition and period and a random participant intercept. Confirmatory testing follows a hierarchical (gatekeeping) strategy: these outcomes are formally tested only if ≥1 coprimary endpoint is significant after Holm adjustment. Multiplicity across key secondary outcomes controlled using Holm (α=.05). Pairwise condition comparisons use Tukey adjustment.
Key secondary	Does active ETU^j^ lead to better objective sleep outcomes than nondigital activity?	Active ETU will show significant differences in sleep outcomes than nondigital activity.	Active ETU will show no significant differences in sleep outcomes than nondigital activity.	SOL, WASO, SE, TST, Sleep Stages (REM%, Deep%, Light%). LMM with fixed effects for condition and period and a random participant intercept. Confirmatory testing follows a hierarchical (gatekeeping) strategy: these outcomes are formally tested only if ≥1 coprimary endpoint is significant after Holm adjustment. Multiplicity across key secondary outcomes controlled using Holm (α=.05). Pairwise condition comparisons use Tukey adjustment.
Key secondary	Are there differences in subjective sleep quality across passive ETU, active ETU, and nondigital activity?	Subjective sleep quality will differ across conditions.	Subjective sleep quality does not differ across conditions.	Single-Item Sleep Quality (0‐10). Exploratory Analysis using LMM with fixed effects for condition and period (and sequence if included) and a random intercept for participant. Report model-based estimated marginal means for each condition and pairwise contrasts with Tukey-adjusted 95% CIs (*P* values reported descriptively)
Secondary	What do participants’ adherence to the assigned evening activity and their perceived experience of the activity look like over the study?	Dropout and nonadherence rates will be higher in the active ETU condition compared with passive and nondigital activity.	Dropout and nonadherence rates are equal across all 3 conditions.	Adherence: % of nights with ≥30 min activity; mean engagement time. Exploratory Analysis using LMM with fixed effects for condition and period (and sequence if included) and a random intercept for participant.
Implementation	What is the overall comfort/usability of the MUSE EEG headband during sleep?	(Exploratory, no formal hypothesis)	Not applicable	Comfort rating (1‐5 Likert). Exploratory/descriptive only. Report mean (SD), median (IQR), % nights rated ≥4.

a WASO: wake after sleep onset.

b SOL: sleep onset latency.

c EEG: electroencephalography.

d Passive ETU: passive evening technology use (watching a documentary on SVT PLAY app).

e SE: sleep efficiency.

f TST: total sleep time.

g REM: rapid eye movement.

h LMM: linear mixed-effects model.

i Nondigital activity (reading a book).

j Active ETU: active evening technology use (playing a video game called Ruzzle).

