### Methodological Consideration

This study will use a randomized crossover design. This within-subject approach limits confounding, minimizes the influence of inter-individual variability, and increases statistical power, which is especially important given the moderate sample size [3,4]. Objective sleep measures will be captured via a wearable EEG headband (MUSE), allowing for naturalistic, at-home sleep tracking that is both minimally intrusive and ecologically valid as it supports generalizability to real-world settings [29]. Additionally, participants will complete daily self-report ratings assessing their subjective sleep quality and mood. Single-item sleep quality measures have limitations because they lack the detail needed to capture the multi-dimensional nature of sleep problems, leading to issues with sensitivity, content validity, and reliability. However, the item is low-burden and has good construct validity [24]. The inclusion of a brief affective experience scale, adapted from validated instruments such as the Visual Analog Mood Scales [25], Positive and Negative Affect Schedule [26], and the User Engagement Scale [27], enables examination of psychological and experiential factors that may mediate the relationship between ETU type and sleep outcomes. Combining objective EEG data with subjective daily logs will provide a holistic, multidimensional understanding of sleep quality [18].

In this randomized crossover trial, participants will receive structured instructions and technical support to guide them in using the EEG headband and completing the assigned activities. These elements are designed to support compliance, usability, and data completeness. In this study design, there is a bias due to the carryover effect (residual effects of one condition influencing the next) and period/sequence effects (time- or order-related differences) [38]. These biases will be mitigated with a one-week washout period and by randomizing condition order, analyzing participant-level week means (which dampens night-to-night variability). This will also help to reduce weekend bias, as weekend sleep might differ from weekday sleep.

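### The coprimary mixed model is given two incompatible units, week means and nights; on nights, a lone participant intercept understates the standard error if nights within a week are correlated

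*Protocol article*

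**What the plan says.** Four statements in the protocol article bear on the unit of analysis.

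- Statistical Analysis Plan, second paragraph: "All analyses will use participant-level week means (nightly values averaged within each intervention week/condition".
- The end of the same paragraph says that these week means "will be calculated for descriptive purposes".
- Statistical Analysis Plan, paragraph on the coprimary outcomes: "The LMM analyses will use all available valid nights".
- Discussion, Methodological Consideration, among the measures against bias: "analyzing participant-level week means (which dampens night-to-night variability".

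The model is the same wherever it appears: "we will fit an LMM with fixed effects for condition and period and a participant-specific random intercept". The Abstract and Table 1 repeat it without naming a unit. The primary comparison, combined ETU against nondigital activity, is "tested as a prespecified linear contrast of the condition marginal means from a linear mixed-effects model (LMM". SOL and WASO are then tested "using the Holm procedure with a family-wise α of .05 (2-sided", and one significant coprimary result opens confirmatory testing of the key secondary outcomes, which use the same model. Under Study Design, each condition occupies one whole week, in one of six randomised sequences.

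**The concern.** The first and fourth statements make the week mean the unit of inference; the second and third make it the night. The coprimary test is therefore not uniquely defined.

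The choice matters because only one random effect is specified. Condition is randomised to a participant's week, so the participant-week is the experimental unit. Nights in the same week can share illness, stress or the person's own response to that condition. Each participant receives each condition in exactly one period, so that personal response is also variation at participant-by-period level. With week means, the residual of the stated model is at the level that was randomised. With nights, the shared variation goes into a residual treated as independent from night to night, and up to seven nights count as seven replicates of the condition.

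At stake are the confidence intervals for the primary contrast, the p-values passed to Holm, and the gate to the key secondary outcomes.

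**Working it through.** **Inputs from the article.** 55 participants, 3 one-week periods, 6 sequences, up to m = 7 nights per condition, two-sided family-wise α of .05 with Holm over two outcomes. The sample size itself cannot be reproduced, because the power inputs are in Multimedia Appendix 1, which is not shown. This check does not need them.

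**Assumed input.** Let r be the share of within-person night variance that lies between weeks. The article gives no value, so r runs from 0 to 0.20. Scale the variances as s_w² = r (week) and s_e² = 1 − r (night).

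**Formulas.** The contrast has weights ½, ½ and −1, whose squares sum to 1.5.

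- True variance per participant: 1.5 × (s_w² + s_e²/m).
- Variance assumed by the night-level model with a participant intercept only: 1.5 × MS/m, where MS = [2(s_e² + m·s_w²) + (3m − 3)s_e²]/(3m − 1). This pools 2 between-week and 3m − 3 within-week degrees of freedom.
- Variance ratio: VR = (s_e² + m·s_w²)/MS.
- Type I error: 2 × [1 − Φ(z/√VR)], with z the two-sided critical value.

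**Worked case, r = 0.10, m = 7.** MS = [2(0.9 + 0.7) + 18 × 0.9]/20 = 19.4/20 = 0.97. VR = 1.6/0.97 = 1.649, and √VR = 1.284. Then 1.960/1.284 = 1.526, which gives a two-sided type I error of .127.

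| r | VR | true SE / model SE | type I at .05 | type I at .025 | at least one false coprimary rejection |
|---|---|---|---|---|---|
| 0 | 1.000 | 1.00 | .050 | .025 | .049 |
| 0.02 | 1.127 | 1.06 | .065 | .035 | .068 |
| 0.05 | 1.320 | 1.15 | .088 | .051 | .100 |
| 0.10 | 1.649 | 1.28 | .127 | .081 | .155 |
| 0.20 | 2.340 | 1.53 | .200 | .143 | .265 |

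The last column is 1 − (1 − a)², with a the type I error at Holm's first step of .025. It takes both null hypotheses as true and SOL and WASO as independent. For r = 0.10: 1 − (1 − .0809)² = .155.

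**Fewer valid nights.** With 5 per week, type I error at .05 is .076 for r = 0.05 and .103 for r = 0.10. With 4, it is .070 and .090.

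**Simulation.** 3,000 trials per setting, 55 participants, 6 sequences, 7 nights, fixed condition and period, with within-participant centring standing in for the random intercept. The Monte Carlo standard error near .05 is √(.05 × .95/3000) = .004.

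| Within-week dependence | nights | week means |
|---|---|---|
| r = 0 | .054 | .053 |
| r = 0.05 | .086 | .048 |
| r = 0.10 | .128 | .055 |
| r = 0.20 | .210 | .053 |
| r = 0, AR(1) of 0.1 between nights | .072 | .046 |
| r = 0, AR(1) of 0.2 | .107 | .053 |
| r = 0, AR(1) of 0.3 | .137 | .049 |

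The simulation agrees with the formula on nights and shows week means at the nominal level throughout.

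**The case against.** The strongest reply is that two of the four statements put the analysis on week means, where the stated model is valid. Inflation then needs two conditions: that nights are analysed, and that nights within a week are correlated. The article gives no correlation, and at r = 0 the error is .050. This stands. What is certain from the text is the conflict over the unit; the inflated error belongs to one branch of it.

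A second reply is that an article condenses a fuller plan. Condensing can explain an omission, but here two incompatible statements are both printed. The sentence that all valid nights enter the analysis fits either unit, so it settles nothing. The general check of model assumptions names only transformation or a generalized mixed model as remedies, neither of which adds a week-level term. Masked condition labels limit choosing the unit by the direction of a result, but they do not say which unit is primary.

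A reader might also infer three stronger points, which the documents do not support:

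- **That unweighted week means are a comparable fault**, because a week with one valid night counts as much as a week with seven. With valid-night counts that varied widely but were unrelated to condition, simulated type I error stayed between .042 and .063 (1,200 trials per setting), and the standard error was about 2% to 8% larger than with weighting. That is a modest loss of precision.
- **That a weekend term is required.** Every seven-day period contains the same weekdays. Missing nights would bias the contrast through weekends only if weekend loss differed by condition, and nothing in the article suggests that it does.
- **That week means weighted by the number of valid nights reproduce a correct nightly model.** Such weights assume zero between-week variance. The matching weight is 1/(s_w² + s_e²/n), with n the number of valid nights.

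**Conclusion.** The contradiction is explicit in current text, nothing in the article reconciles it, and it leaves the confirmatory test undefined. If the night-level sentence is followed literally with the stated random effect, the standard error of the ETU contrast is too small whenever within-week correlation is above zero.

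The size rests on the assumed r. With seven nights, per-test error at nominal .05 runs from .050 at r = 0 to .200 at r = 0.20, and is smaller with fewer valid nights. Under independence of the two outcomes, the chance of wrongly opening the secondary gate runs from .049 to .265 over the same range.

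It would be too strong to say that the trial's type I error is inflated. The article does not settle which unit will be used and gives no within-week correlation. Some positive correlation is plausible, but its size is unknown.

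**What to change.** Before unmasking, and preferably before the masked analysis starts, name one unit for the primary and key secondary mixed models. Align both Statistical Analysis Plan paragraphs and the Methodological Consideration text with it. Either choice below is sound:

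1. **Nights**, with fixed condition and period and random intercepts for participant and for participant-by-period. Week means then remain descriptive, and the sentence committing all analyses to them is removed, as is the Discussion's reliance on them.
2. **Week means**, with fixed condition and period and a participant intercept. The sentence putting the mixed models on all valid nights, and the one making week means descriptive, are then reworded.

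No new data are needed. The change is a sentence or two of text and, for nights, one additional random term in the syntax. Confidence intervals will be somewhat wider than those from the night-level model as written, to the extent that nights within a week are correlated.

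### Opening the key secondary family at a full .05 after only one Holm-tested coprimary succeeds uses the same alpha twice; family-wise error can approach .10

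*Protocol article*

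**What the plan says.** The Statistical Analysis Plan section of the protocol article defines two confirmatory families.

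- **Coprimary family.** "The coprimary outcomes are SOL and WASO derived from the MUSE EEG". Control across the two "coprimary endpoints (SOL and WASO) will be performed using the Holm procedure with a family-wise α of .05 (2-sided").
- **Gate.** "If at least one coprimary endpoint is statistically significant after the Holm adjustment, we will proceed to confirmatory testing" of the key secondary outcomes. If neither coprimary is significant, the secondaries are reported as exploratory.
- **Key secondary family.** The text lists five outcomes: total sleep time (TST), sleep efficiency (SE), and the REM, deep and light percentages. Their P values are "adjusted using Holm’s procedure (2-sided α=.05), applied only if the gatekeeping criterion on the coprimary outcomes is met".

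The three objective-outcome rows of Table 1 marked as key secondary repeat the rule ("these outcomes are formally tested only if ≥1 coprimary endpoint is significant after Holm adjustment"), call it a hierarchical gatekeeping strategy, and again give Holm at .05. Nothing in the document lowers the secondary alpha when only one coprimary is significant.

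**The concern.** With two endpoints, Holm tests the smaller P value at .025 and, if that is rejected, the other at .05. The alpha freed by the first rejection goes to the remaining coprimary. It becomes available to another family only when that second hypothesis is rejected too.

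The plan uses it in both places after a single rejection: .05 for the second coprimary and .05 for the secondary family. Each piece is valid alone, but the combination does not control error across the two families.

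What is at stake is the word confirmatory for secondary findings after a split result, where only SOL or only WASO is significant. SOL and WASO measure different things and the gate itself anticipates such a result, so this is a realistic outcome.

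**Working it through.** **Inputs from the protocol:** two coprimaries; Holm at two-sided .05; gate at one or more; five key secondaries; Holm at two-sided .05.

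**Assumptions, because the protocol gives no figures:** one test per secondary outcome; equal correlation among the normal test statistics; power of the truly affected coprimary.

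**Step 1. The plan's own figure.** With both coprimaries null, Holm errs only if the smaller P value is at or below .025. The bound is .025 + .025 = .05, and under independence the error is 1 − .975² = .0494. The stated .05 for the coprimary family is correct.

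**Step 2. Where the two families together can fail.**

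- *Both coprimaries null:* the gate opens only after a coprimary error has occurred, so the secondaries add nothing. Error ≤ .05.
- *Both coprimaries real:* only the secondary family can err. Error ≤ .05 (.0490 under independence, from 1 − .99⁵).
- *Exactly one null:* the real effect opens the gate, the null coprimary is tested at .05, and the secondaries get another .05. This is the failing case.

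**Step 3. Size in the failing case, real effect surely detected, all secondaries null.**

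- Upper bound: .05 + .05 = .10.
- Independent statistics, Holm over five secondaries (first step .05/5 = .01): 1 − .95 × .99⁵ = 1 − .95 × .95099 = .0966.

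**Step 4. Lower power.** If the real coprimary is rejected at .025 with probability .80, then under independence the error is .80 × .0966 + .20 × .025 = .0822. The second term is the case where the gate can open only through a false rejection at .025. At 90% power, .90 × .0966 + .10 × .025 = .0894.

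**Step 5. Correlation.** Simulation with 400,000 draws:

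| Common correlation | Power near 1 | Power 80% |
|---|---|---|
| 0 | .096 | .082 |
| .3 | .091 | .075 |
| .5 | .082 | .063 |
| .7 | .070 | .051 |

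At correlation .8 the figures are .062 and .045.

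**Step 6. The remedies in the same failing case.**

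- *Both coprimaries required:* a secondary claim can be made only after the null coprimary has been falsely rejected at .05, so the error is exactly .05 when the real effect is surely detected. The largest simulated value over all configurations was .0508, which reflects simulation error.
- *Each coprimary at .025, passing on only released alpha:* 1 − .975 × (1 − .025/5)⁵ = 1 − .975 × .97525 = .0491 under independence (simulated .0487).

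**The case against.** Four points deserve weight.

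**No overall alpha is stated.** The protocol gives .05 for each family and never one rate for both, so no explicit promise is broken. That is true. But the protocol calls the secondary tests confirmatory and links the families by gatekeeping, whose purpose is to carry error control from one family to the next. If .05 per family were all that was meant, the gate would have no function.

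**The all-null secondary scenario is artificial.** SE is TST over time in bed, and recording starts at lights-out. If SOL lengthens while WASO and TST do not change, SE must fall. The stage percentages are also compositional if taken as shares of sleep, so full independence is not attainable. Both points are fair, but they barely change the size. If SE is real and surely rejected, Holm relaxes to .05/4 = .0125 for the other four, giving 1 − .95 × .9875⁴ = .0966 under independence. A simulation with SE tied to its components and compositional stages, under assumed variances and correlations, gave .070–.073 at 80% power for SOL, .079–.084 at 95% and .084–.089 near 100%.

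**The inflation is conditional.** It needs exactly one null coprimary and shrinks with lower power or strong correlation, falling below .05 at 80% power and correlation .8. This stands: the near-doubling is a worst case.

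**The primary conclusions are safe.** This also stands. Only the status of secondary claims after a split result is affected.

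**Conclusion.** The concern holds. The gate, as written in the text and in Table 1, does not control error across the coprimary and key secondary families. When exactly one coprimary has a real effect, the probability of at least one false confirmatory claim can reach about .097 (bound .10) where .05 is the level set for each family. Over assumed correlations from 0 to .7 it runs from .096 to .070 with power near 1, and from .082 to .051 at 80% power. The correlations, the power and the single test per secondary outcome are assumptions. That the same alpha is spent twice follows from the stated rule alone.

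**What to change.** **Preferred:** keep Holm for SOL and WASO, and open the key secondary family at .05 only if both are significant. Change the gate sentence in the Statistical Analysis Plan section and the three objective-outcome key secondary rows of Table 1 together.

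**Alternative, if the sponsor wants the gate to open after one success:** test SOL and WASO at .025 each (Bonferroni, no reuse within the pair). Apply Holm across the secondaries at .025 if one is significant and at .05 if both are. The primary-objective row of Table 1 also names Holm and would need the same edit.

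Under either option, state which hypotheses form the secondary family. The text lists five outcomes, while the Table 1 rows also include SOL and WASO and cover three pairwise contrasts.

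**Cost:** wording only, with no new data. Under the preferred option the secondaries become exploratory after a split result. Under the alternative the second coprimary is tested at .025 instead of .05, and the secondaries have less power after one success. Data collection is projected to end in spring 2027 and the analysts work on masked labels, so the change can be made before any result is known.
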